### Adverse Events Reporting

**Definitions of an adverse event**

An adverse event (AE) is defined as "any untoward medical occurrence in a participant administered a pharmaceutical product that does not necessarily have a causal relationship with this treatment" Examples of adverse events include but are not limited to:

1. Worsening of conditions present after the intake of medicine (magnesium sulphate)
2. Events related or possibly related to concomitant medications
3. Hypersensitivity to magnesium sulphate
4. Signs and symptoms resulting from drug overdose
5. Any other significant complication

A serious adverse event (SAE) is defined as an experience that results in any of the following outcomes:

1. Death during the period of study follow-up
2. Life-threatening experience (one that puts a participant at immediate risk of death at the time of the event)
3. Prolonged hospitalization during the period of study follow-up
4. Persistent or significant disability or incapacity
5. Specific medical or surgical intervention to prevent one of the other serious outcomes listed in the definition.

**Reporting of serious adverse events**

For each serious adverse event identified and graded as moderate, severe or life threatening, a serious adverse event report form will be completed (SOMREC form).

The adverse events will be documented and submitted to the IRB with the annual report while the serious adverse events will be reported in 24 hrs and then full report within 5 working days. Guidelines for reporting of serious adverse events provided by the Makerere University School of Medicine Research and Ethics Committee, the Ugandan National Council for Science and Technology.

**Management of adverse events**

All adverse events regardless of the suspected causal relationship to the investigational product will reported to the PI. A physician attached to the study will treat the adverse event in consultation with the attending obstetrician on duty. Participant requiring more specialized care will be linked to care within or out of the hospital. The PI will assess the SAE causal relationship to the study device, follow up the participant until the event or sequelae has resolved or stabilized to a level acceptable to the IRB and data safety monitoring board.

#### Stopping rules

#### Stopping will be implemented if the use of the Springfusor for administration of magnesium sulphate becomes a national policy or if at the interim review, the acceptability of the Springfusor for the administration of magnesium sulphate is superior than the standard of care or, there significant complications in the Springfusor arm. However, during the accrual of the study, when the cases experiencing respiratory depression due to magnesium sulphate toxicity in the Springfusor arm exceeds 12.5%, an emergency DSMB meeting will be called to review if the study is to stop.

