### Sample size

In the Mundle et al trial[[16](#_ENREF_16)], the Pritchard regimen (IM maintenance) the acceptability of magnesium sulphate was 31%. We are assuming that the women in Springfusor are likely to find magnesium sulphate administration more acceptable by 50%. With power of 90 and alpha of 0.05, we estimate that we need 219 women with preeclampsia in each arm. With approximately 10% non-response, we need 241 women in each arm.

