**Data analysis**

Data analysis will be performed by the PI. Descriptive statistics will be used to summarize baseline characteristics of study participants and assess if randomization was successful. The baseline characteristics will too give guidance as to which variables need to be adjusted for in the final analysis.

Acceptability and safety data will be evaluated using intention-to-treat (ITT) analysis. For comparing the maternal health outcome between intervention and control arms, the main analyses will look at the following variables;

1. Proportion of study participants who regarded magnesium sulphate administration using Springfusor or Pritchard route was acceptable. This will be compared using chi-square.
2. *Rate of complications of preeclampsia and its management:* Proportion of preeclamptic and eclamptic women who developed magnesium sulphate toxicity, abnormal liver and renal function test, infection at the injection and maternal deaths
3. The intensity of pain will be analysed using a ttest and presented as means and standard deviation
4. *Feasibility of Springfusor pump use:* The proportion of women who have a Springfusor used for the administration of magnesium sulphate and experience some technical problem with its use, blockage of FCT, the number of attempts made prior to successful Springfusor placement, the number of failed Springfusor placement and the number of FCTs used and spilled magnesium sulphate.
5. *The reliability of the springfusor:* The intra-class correlation coefficient (ICC) will be calculated. The closer the ICC to 1, the higher the reliability, ICC <0.4; the poor the reliability and ICC 0.4-0.75; the fair the reliability.

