# Safety and monitoring

The following mechanisms will be employed to ensure the data quality and integrity of the study. An independent data and safety monitoring board (DSMB) will be established to review the data and make recommendations to investigators concerning study continuation and study modification. The main purpose of the DSMB is to ensure that the study participants are not exposed to undue risk. The DMSB will be called upon to review reported serious adverse events and provide advice on management of the study with relation to risk, and will help assure the continued scientific validity and merit of the study. An interim analysis will be conducted in the study when 2/3 of participants have been recruited. Based on the analysis and if deemed necessary, the DSMB will be asked to provide recommendations on study modification. All data analyzed by the DSMB will be reviewed in strict confidence.

The DSMB will consist of three professionals whose combined experience covers the fields of obstetrics and gynaecology, preeclampsia and eclampsia, biostatistics, and ethical conduct of human subject research. Qualifications for selection include: 1) Expertise in the fields of interest, 2) Experience in conduct of clinical trials and statistical knowledge, 3) independence from the direct management of the clinical trial, 4) no financial, scientific or other conflict of interest. Signed conflict of interest statements from each board member must be on the file at PI office prior to initiating DSMB activities.

Accountability log will be used to track the use of Springfusor devices and FCTs during the study. The product will be stored in accordance with the requirements of Springfusor. Any unused Springfusor and FCTs will be held at Mulago Hospital until final instructions are received from Go Medical Ltd.

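### The protocol commits to stopping for superior acceptability at two thirds of recruitment but sets no boundary, while its sample size spends the whole 0.05 on a single look

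*Protocol*

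**What the plan says.** Four sections of the Protocol bear on this.

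- **Stopping rules.** Stopping is worded as something that will happen, and one trigger is "if at the interim review, the acceptability of the Springfusor for the administration of magnesium sulphate is superior than the standard of care". Acceptability is the primary outcome (Outcome Measures). No p-value, Z boundary or spending function is given. The respiratory-depression trigger in the same section does have a number, 12.5%.
- **Safety and monitoring.** "An interim analysis will be conducted in the study when 2/3 of participants have been recruited". The DSMB is then asked for recommendations on modifying the study, but only where this is thought necessary.
- **Sample size.** "With power of 90 and alpha of 0.05, we estimate that we need 219 women with preeclampsia in each arm". The control rate is 31 per cent and the assumed improvement is 50 per cent. Then: "With approximately 10% non-response, we need 241 women in each arm".
- **Data analysis.** For the proportion who found the method acceptable: "This will be compared using chi-square". No allowance is made for an earlier look.

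**The concern.** A rule that ends the trial on the primary outcome is part of the test of that outcome. Without a boundary, the type I error of the whole procedure is unknown. With the conventional 0.05 at each look, it is above the 0.05 that the sample size assumes.

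The second consequence is the amount of data. Complications and device reliability are secondary objectives, and safety is named in the abstract's objective. An easily met superiority stop would cut those data by a third.

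**Working it through.** **1. Reproduce the stated sample size.** Inputs from Sample size: p1 = 0.31; p2 = 0.31 × 1.5 = 0.465; δ = 0.155; mean p̄ = 0.3875; alpha 0.05; power 90%. Sidedness is not stated; two-sided is tried first.

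n = [1.960·√(2p̄(1−p̄)) + 1.282·√(p1(1−p1) + p2(1−p2))]² / δ²
= (1.3504 + 0.8717)² / 0.155² = 205.5, so 206 per arm.

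With continuity correction: n' = (n/4)·[1 + √(1 + 4/(nδ))]² = 218.2, so **219 per arm**, the stated figure. One-sided versions give 168, or 180 with the correction. Then 219 × 1.10 = 240.9, so 241. The stated number is therefore a single-look, two-sided 0.05 calculation with nothing set aside for an interim test.

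**2. Interim size.** 2/3 × 241 ≈ 161 per arm recruited; with 10% non-response, 161 × 0.9 ≈ 145 evaluable. The outcome is taken before discharge, so recruitment is a fair stand-in for information, and the fraction is taken as t = 2/3.

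**3. Type I error.** Under the null, the interim and final statistics (Z1, Z2) are bivariate normal with correlation √(2/3) = 0.816. Assume *superior* means Z1 > 1.96 and the final test is |Z2| > 1.96.

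- Springfusor wrongly declared superior: P(Z1 > 1.96 or Z2 > 1.96) = 0.0385, against 0.025 for one look.
- Wrong finding the other way, possible only at the end: P(Z1 ≤ 1.96 and Z2 < −1.96) = 0.0250.
- Overall: 0.0385 + 0.0250 = **0.0635**.

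A binomial simulation (400,000 trials, 161 then 241 per arm, common rate 0.31 or 0.3875) gave 6.4% and 6.3%.

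| Reading of the interim rule | Overall error, final two-sided 0.05 |
|---|---|
| p<0.05, stop only for Springfusor | 6.3% |
| one-sided 0.05, stop only for Springfusor | 8.4% |
| p<0.05, stop in either direction | 7.7% |
| p<0.001 | 5.0% |

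**4. Superior read as numerically higher (Z1 > 0).** The trial stops early about half the time under the null. If the chi-square is then run at 0.05 on the data in hand, the error has three parts: 0.0250 (upper tail at the interim), 0.00002 (upper tail at the end after Z1 ≤ 0) and 0.02498 (lower tail at the end). The total is 0.0500. The error exceeds 5% only if the numerical difference is itself taken as proof.

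**5. Chance of stopping at the planned effect.** Power at the interim = Φ{[δ√n − z·√(2p̄(1−p̄))] / √(p1(1−p1) + p2(1−p2))}, with δ replaced by δ − 1/n under continuity correction. The two root terms are 0.689 and 0.680. Example, n = 161, z = 1.96, no correction: (1.967 − 1.350)/0.680 = 0.906, so 0.818.

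| Interim threshold | n=161, no correction | n=161, corrected | n=145, no correction | n=145, corrected |
|---|---|---|---|---|
| p<0.05 | 82% | 79% | 78% | 74% |
| p<0.0121 | 64% | 59% | 58% | 53% |
| p<0.001 | 33% | 29% | 28% | 24% |

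**6. Safety precision lost.** The upper 95% bound for an event never seen is 1 − 0.05^(1/n): 1.8% with 161 women on Springfusor, 1.2% with 241.

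**The case against.** The best defence is that boundaries often sit in an SAP or DSMB charter, neither of which is shown, and that a strict one would leave the error at 5.0%. This stands to the extent that every figure above 5% depends on an assumed interim threshold. It does not remove the point: the protocol itself fixes the superiority stop, gives no threshold and refers to no other document for one.

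It can also be said that the stop may not be automatic, since Safety and monitoring gives the DSMB an advisory role. That is fair. The two sections differ on whether the rule binds, so the early-stop probabilities apply only if it is carried out as written.

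Four stronger readings are tempting, and the text does not carry them.

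- **An error of 7.7%.** That needs a stop in either direction; the rule stops only in Springfusor's favour.
- **A false-positive rate of 50%.** That is the chance of stopping early under the null on a numerical lead. The claim rests on the chi-square, and no section treats a numerical lead as proof.
- **A breach of interim confidentiality by the investigator.** Data analysis does say "Data analysis will be performed by the PI", but nothing says that person runs the interim comparison, and the confidentiality promise concerns data analysed by the DSMB.
- **No ethical case for an early stop on a subjective open-label rating.** That is a judgement, and the point does not need it.

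The safety loss is also modest, and the respiratory-depression trigger operates throughout accrual in any case.

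**Conclusion.** The point holds. The protocol commits to a superiority stop on its primary outcome without a boundary, and its sample size and final test are those of a single-look design.

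With the ordinary 0.05 test at both looks and stopping only for Springfusor, the overall error is about 6.3%, and the error in Springfusor's favour is about 3.8% instead of 2.5%. This assumes information of 2/3 at the interim and a two-sided final test. If *superior* means numerically higher, the damage is lost power and precision: a comparison planned for 90% power would be made at the interim with about 74–82%.

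On the sponsor's own effect assumption, a p<0.05 rule applied as written would probably end the trial with two thirds of the safety and reliability data. The inflation is moderate, but it affects the primary claim and should be settled before any interim data are seen, because a boundary chosen afterwards cannot restore the error rate.

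**What to change.** Under Stopping rules and Safety and monitoring, adopt one of these:

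1. Stop for superiority only if the interim comparison favours Springfusor at two-sided p<0.001, with the final test at about 0.05 (0.0499 if exactness is wanted). Overall error 5.0%.
2. Use an alpha-spending boundary, for example O'Brien-Fleming type: interim p<0.0121 (|Z|>2.509), final p<0.0463 (|Z|>1.993). Power at 219 per arm falls from 91.5% to 91.2% (normal approximation, no continuity correction); about 222 per arm restores it, within the 241 to be recruited.
3. Delete the superiority stop and keep the interim for safety only.

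In each case, reconcile the two sections on whether a crossed boundary obliges the trial to stop or only informs the DSMB's recommendation.

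The cost is one or two sentences, no extra participants and almost no final power. The downside is a lower chance of stopping early at the planned effect: about 24–33% under option 1 and 53–64% under option 2, against 74–82% at p<0.05.

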### Outcome Measures

Primary outcome:

- Acceptability of Springfusor for administration of magnesium sulphate will be assessed using a Likert scale ranging from one (very acceptable) to five (very unacceptable). The method of magnesium sulphate administration is regarded acceptable if its rated 1 and 2 on the likert scale. It is not acceptable if the ranking is three and above. Women who discontinue the method of administration by choice or due to side effects will be considered in group of unacceptable.

Secondary outcomes:

- *Rate of complications of preeclampsia and its management:* Proportion of preeclamptic women who developed magnesium sulphate toxicity, abnormal liver and renal function test as reported by the laboratory report, infection at the injection as reported by the clinician and maternal deaths
- Discontinuation: This will be assessed as study participants who do not completed doses of magnesium sulphate in 24 hour period of including the loading dose. Participants who discontinue the method of administration by choice, due to side effects or by health workers decision will be considered in group. This will be measured by the number of dose received for each arm. For the Pritchard arm (standard of care), the number of complete 6 doses equivalent to 29 gm (including loading dose) in 24 hours. In the Springfusor, the number of complete 6 doses equivalent to 24 gm (including loading dose) in 24 hours.
- *Level of pain:* The study participants will be asked to assess the severity of pain during the administration of magnesium sulphate using Visual analogue scale 1-7. The least (one) representing no pain and maximum (7) representing the worst pain imaginable.
- Safety of use of Springfusor will be assessed by evaluating the possible occurrence of magnesium sulphate toxicity. This will be assessed by occurrence of any of the following
  - respiratory depression<16/min,
  - respiratory arrest,
  - depressed patellar reflex,
  - liver failure, renal failure,
  - cardiac arrest,
  - a need for calcium gluconate.
- In addition, other side effects of magnesium sulphate like nausea, vomiting, flushing of the skin, muscle weakness, confusion and drowsiness will be noted.
- *Feasibility of Springfusor pump use: ⃰* The proportion of women who have a Springfusor used for administration of magnesium sulphate and experience some technical problem with its use, blockage of FCT, the number of attempts made prior to successful Springfusor placement, the number of failed Springfusor placement and the number of FCTs and spilled magnesium sulphate used will also be documented.
- The *reliability** of the Springfusor to administer magnesium sulphate in the prescribed time will assessed for the loading period and the maintenance period. The intra-correlation coefficient for the device will be calculated.

These outcomes will be compared between the women in the two arms. A *outcome will be reported only for women who will have magnesium sulphate administered using Springfusor

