## Research questions

1. Acceptability:
   1. What is the overall acceptability of Springfusor use among women with preeclampsia and eclampsia?
   2. What is the acceptability of the springfusor use for magnesium sulphate administration among health providers
   3. What is the level of pain associated with using Springfusor compared to the standard of care in administration of magnesium sulphate?
2. Effectiveness of Springfusor:
   1. What is the discontinuation rate of magnesium sulphate administration using a Springfusor pump compared to standard of care?
3. Safety
   1. What is rate of complications in the two arms?

Hypothesis

Use of Springfusor pump in the administration of magnesium sulphate in women admitted with preeclampsia and eclampsia is more acceptable than the hospital standard practice

Objectives

Primary objective

1. To compare the acceptability of the Springfusor pump to the standard of care in the administration of magnesium sulphate.

Secondary objective

1. To compare the proportion of complications between the Springfusor pump and the standard of care groups
2. To determine level of pain associated with using Springfusor compared to the standard of care?
3. To determine the discontinuation rate of administration of magnesium sulphate among women admitted with preeclampsia and eclampsia
4. To assess the reliability of Springfusor pump in the delivery of magnesium sulphate when used repeatedly
5. To assess the acceptability of the Springfusor pump for the administration of magnesium sulphate among the health providers.

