### Intervention

Women in the intervention arm (Springfusor group) will have their loading and maintenance therapy of magnesium sulphate using IV infusion administered using a Springfusor infusion pump. The loading dose will be 4 gm of 50% magnesium sulphate in 10 ml syringe administered over 20 mins. The maintenance dose of 4 gm of 50% magnesium sulphate in 10 ml will administered over 4 hours. The 4 gm dose will be repeated every 4 hours for 24 hours

Women in the control arm (Standard of care group) will have magnesium sulphate administered according to the standard hospital practice. The loading dose of is administered using an IV-push in which health worker manually and slowly inject 4 gm of 20% Magnesium sulphate in 20 ml syringe over 15-20 minutes. This is immediately followed by IM injection of 10 gm of 50% magnesium sulphate and 1 ml of lignocaine into the gluteal muscles (5 gm on each buttocks). The maintenance dose of 5 gm IM injection every 4 hourly for 24 hours. Over the 24 hour period the intravenous group (intervention) would have got 28 gm of magnesium sulphate while the intramuscular group (control) would have received 39 gms. The higher total dose in the control group is assuming a reduce bioavailability of intramuscular drug.

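### The control completion threshold for discontinuation is given as 29 gm, but six doses of the stated regimen make 39 gm; the Springfusor 24 gm is not reconciled with the 28 gm course

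*Protocol*

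**What the plan says.** The Outcome Measures section of the protocol defines discontinuation as failure to complete the magnesium sulphate doses within 24 hours. On the measure it says: "This will be measured by the number of dose received for each arm". For the control (Pritchard) arm, completion is "the number of complete 6 doses equivalent to 29 gm (including loading dose) in 24 hours". For the other arm: "In the Springfusor, the number of complete 6 doses equivalent to 24 gm (including loading dose) in 24 hours". A separate clause classes some women as discontinued whatever they received: "Participants who discontinue the method of administration by choice, due to side effects or by health workers decision will be considered in group".

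The Intervention section sets out the regimens. Control women receive 4 gm IV. "This is immediately followed by IM injection of 10 gm of 50% magnesium sulphate", given as 5 gm in each buttock, and 5 gm IM follows every 4 hours. Springfusor women receive a 4 gm load over 20 minutes and then 4 gm syringes, each run over 4 hours: "The 4 gm dose will be repeated every 4 hours for 24 hours". The section totals both courses over 24 hours: "the intravenous group (intervention) would have got 28 gm of magnesium sulphate while the intramuscular group (control) would have received 39 gms".

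Under Research questions, one question is listed for effectiveness: "What is the discontinuation rate of magnesium sulphate administration using a Springfusor pump compared to standard of care". Outcome Measures adds that outcomes are compared between the two arms, apart from those marked as Springfusor-only. Discontinuation is not so marked.

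**The concern.** The two sections give different amounts for what should be the same course. In the control arm, six doses with loading counted are 29 gm in one place and 39 gm in the other. In the Springfusor arm, completion is 24 gm in one place and the 24-hour course is 28 gm in the other.

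The gram figure matters even though the stated measure is a dose count, because within the outcome definition it is the only statement of what the six control doses contain. A control woman who never received the 10 gm IM loading injection matches the stated 29 gm exactly. If staff apply the grams directly, a control woman who missed two of her five maintenance injections also counts as complete. Either error would occur in one arm only, in an outcome that is compared between arms.

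In the Springfusor arm the question is whether a sixth maintenance syringe is scheduled. If it is, the dose-count rule lets a Springfusor woman miss one dose of seven, while a control woman may miss none of six.

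**Working it through.** **Inputs** (protocol, Intervention and Outcome Measures)

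- Control loading: 4 gm IV + 10 gm IM = 14 gm. Maintenance: 5 gm every 4 hours. Stated 24-hour total: 39 gm.
- Springfusor loading: 4 gm over 20 minutes. Maintenance: 4 gm per 4-hour syringe, so 1 gm per hour. Stated 24-hour total: 28 gm.
- Stated completion: six doses with loading counted, 29 gm for control and 24 gm for Springfusor.

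**Formula.** Total = loading dose + (number of doses − 1) × maintenance dose.

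**Control, six doses.** 14 + 5 × 5 = 39 gm. This reproduces the Intervention total and does not reproduce 29 gm. The shortfall is 39 − 29 = 10 gm, and 29/39 = 74.4%.

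**Where 29 gm could come from**

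| Reading | Sum | Result |
|---|---|---|
| IV part of loading only, plus five injections | 4 + 5 × 5 | 29 gm, with the 10 gm IM loading omitted |
| Each administration counted as a dose (one IV, two buttock injections, three maintenance) | 4 + 5 + 5 + 3 × 5 | 29 gm, but only three maintenance injections |
| IM loading counted as a dose of its own | 4 + 10 + 4 × 5 | 34 gm, not 29 |

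The first reading leaves out part of the loading dose. The second fits poorly with a 24-hour course. Neither is the course in the Intervention section.

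**When a control woman reaches 29 gm.** Assume the first maintenance injection is at hour 4.

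| Hour | 0 | 4 | 8 | 12 | 16 | 20 |
|---|---|---|---|---|---|---|
| Cumulative gm | 14 | 19 | 24 | 29 | 34 | 39 |

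Read in grams, the threshold is met at hour 12 with two of five injections still due.

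**Springfusor.** Six doses: 4 + 5 × 4 = 24 gm, so the completion rule is correct within itself. The Intervention total of 28 gm is 4 + 6 × 4, which is seven doses. The threshold is 24/28 = 85.7% of that course, one syringe short. The Intervention section therefore counts six doses for control and seven for Springfusor over the same 24 hours. On seven doses the control total would be 14 + 6 × 5 = 44 gm.

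**Timing.** Assume syringes run back to back after the load.

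- The fifth ends at 20 min + 5 × 4 h = 20 h 20 min.
- The sixth ends at 20 min + 6 × 4 h = 24 h 20 min.
- Infused by hour 24: 4 + 23.67 h × 1 gm/h = 27.67 gm.

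By hour 24 about 27.7 gm has been given, but only loading plus five syringes (24 gm) is complete. That would reconcile the two figures if only doses completed within 24 hours count. The protocol does not say whether this is meant.

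**The case against.** The strongest reply is that the operative rule is the dose count, six in each arm, and the grams are only a gloss. Six control doses with the full loading dose are exactly the 39 gm course, so a reader who ignores the gram figure classifies control women correctly. The regimen is also described in several places with the IM injection directly after the IV dose, so trained staff are unlikely to accept a load without it as complete.

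Second, women who stop by their own decision, because of side effects or on a health worker's decision are discontinued at any dose total. A midwife who chooses to withhold maintenance arguably falls under that clause. Only other missed doses are left to the threshold, and the protocol gives no frequency for them.

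Third, the Springfusor 24 gm is right for six doses, and the timing above offers a consistent reading under which the rule is six of six in both arms.

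Most of this stands and limits the consequence. It does not rescue the 29 gm figure, which contradicts the stated regimen and is corrected nowhere else in the protocol. On the Springfusor side it leaves a clarification to make rather than a proven error, since the document does not choose between the two readings.

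**Conclusion.** The 29 gm threshold is wrong as written: six control doses under the stated regimen are 39 gm. This rests only on the doses in the Intervention section. Taken in grams, the threshold is 74% of the course and tolerates two missed maintenance injections of five; it also equals the whole course without the IM loading injection. The hour-12 timing assumes maintenance starts at hour 4.

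The Springfusor figures of 24 gm and 28 gm are unreconciled. The slack is one syringe if six are scheduled after loading, and none if five are, or if only syringes completed by hour 24 count.

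Neither the size nor the direction of any effect on the comparison of discontinuation rates can be derived from the protocol. Discontinuation is a secondary outcome; the primary outcome, sample size and stopping rules do not use these thresholds. The point should be fixed, because it is a stated threshold for a between-arm comparison and the only question listed under effectiveness.

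**What to change.** In Outcome Measures, change 29 gm to 39 gm and define completion as receipt of every scheduled dose:

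- **Control:** loading (4 gm IV and 10 gm IM, both required) plus five maintenance injections = 39 gm.
- **Springfusor, choose one:**
  - (a) Loading plus six syringes = 28 gm, counting the last syringe if it was started within 24 hours. This relaxes the present requirement that doses be complete by hour 24, since the sixth syringe ends at 24 h 20 min.
  - (b) Loading plus five syringes = 24 gm, with the 28 gm total and the maintenance wording in the Intervention section changed to match.

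The cost is wording in Outcome Measures, and in the Intervention section under option (b). Doses received are already counted for each woman, so no extra data collection is needed.
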